It is important to study the impact of malnutrition in children because its long-term consequences could be reduced which implies promoting positive effects on oral and general healthy.

The primary aim of this trial is to evaluate the effect of low-level laser on the saliva of children aged 1 to 5 years with energy-protein malnutrition. Secondary outcomes are to establish the degree of malnutrition in children aged 1 to 5 years and to analyze the saliva of children aged 1 to 5 years with energy-protein malnutrition.

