**Table 2 T2:**
[figure not shown]
Normal IgA values in saliva of Brazilian children.

The data will be analyzed using Analysis of Variance (ANOVA) and Pearson's correlation test (*α* = 0.05). The Statistical Package for the Social Sciences (SPSS) (IBM Corp. Released 2012. IBM SPSS Statistics for Windows, Version 21.0. Armonk, NY: IBM Corp) version 15.0 will be used for all analyses.

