### Administration of low level laser

2.9

Low-level laser will be administered using the Photon Lase III device (DMC Equipamentos LTDA, São Paulo, Brazil). Laser will be administered for 10 seconds on 4 intraoral points and 4 extraoral points in the region of the parotid glands bilaterally as well as 1 intraoral point and 1 extraoral point in the regions of the submandibular and sublingual glands. The first session will occur after the collection of saliva. The second and third sessions will be performed 7 and 14 days after the first session, respectively. The final saliva collection will be performed after the third laser session.^[34,35]^

The laser will be adjusted according to the following parameters: Central wavelength (nm) = 808; spectral band width (FWHM) (nm) = 2; operational mode = continuous; mean radiant power (mW) = 100; polarization = randomized; aperture diameter (cm) = 0.2; irradiation at aperture (mW/cm^2^) = 2500; beam profile = multimodal; beam spot on target (cm^2^) = 0.04; irradiation at target (mW/cm^2^) = 2500; exposure time (s) = 40; Radiant exposure (J/cm^2^) = 100.0; radiant energy (J) = 4; number of points irradiated = 10; irradiated area (cm^2^) = 0.40; application method = Contact; number of treatment sessions = 3; frequency of treatment sessions per week = 1; Total radiant energy (J) = 40.

The salivary flow rate and salivary IgA will be compared before and after of each laser application (after 7 and 14 days) and correlation with the malnutrition will be established. The results will be analyzed using ANOVA and Tukey's contrast test. The level of significance will be 5%.

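### The primary aim is served by two unranked tests, flow rate and IgA, each at 5%; if significance on either counts as an effect on saliva, the error rate is up to 9.75%

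*Protocol article*

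**What the plan says.** The Background states the aim as follows: "The primary aim of this trial is to evaluate the effect of low-level laser on the saliva". Saliva is not itself a variable that can be tested. The same paragraph goes on: "Secondary outcomes are to establish the degree of malnutrition in children aged 1 to 5 years", and adds a descriptive analysis of the children's saliva. Neither item ranks flow rate against IgA for the laser question.

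Section 2.9 names the variables for that question: "The salivary flow rate and salivary IgA will be compared before and after of each laser application". On method it says "The results will be analyzed using ANOVA and Tukey's contrast test", and on the error rate "The level of significance will be 5" per cent. The general analysis statement at the end of section 2.8 also uses a level of 0.05: "The data will be analyzed using Analysis of Variance (ANOVA) and Pearson's correlation test".

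The article gives no hierarchy, no split of the 5% between the two variables, and no rule that both must be significant. The abstract also lists flow rate and IgA side by side. Buffering capacity is a third saliva property measured in section 2.8, but it is not in the before/after list of section 2.9.

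**The concern.** One aim is answered by two tests, and each appears to carry the full 5%. The aim is worded broadly enough for a positive result on either variable to be presented as an effect on saliva. In that case the 5% level holds for each test but not for the main conclusion. With no variable named in advance, whichever one moved could become the headline after the data are seen.

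Tukey's test does not help here. It controls the error among pairwise time-point contrasts for one variable and gives no protection across two.

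Multiplicity detail can reasonably sit in an analysis plan that is not shown. Which variable answers the primary aim is a protocol decision, and the article does address it: it states an aim, secondary outcomes, tests and a level. The fault is that these do not fit together.

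**Working it through.** **Inputs**
- Variables in the before/after laser comparison: 2, flow rate and IgA (section 2.9).
- Level: 0.05, with no split (sections 2.8 and 2.9). I read it as applying to each variable's test.
- Correlation between the two test statistics: not given. Assumed range 0 to 0.9 in absolute value.
- Decision rule: not given. The calculation assumes that significance on either variable is read as an effect on saliva.

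**Step 1. The plan's own figure.** With one test, the error is 1 − 0.95 = 5.0%, which matches the stated level.

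**Step 2. Two independent tests.** 1 − 0.95² = 1 − 0.9025 = 9.75%. The upper bound under any dependence is 0.05 + 0.05 = 10%. The ratio to the stated level is 9.75 / 5 = 1.95.

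**Step 3. Two correlated tests.** With a bivariate normal pair, the error is 1 − P(|Z₁| ≤ 1.96 and |Z₂| ≤ 1.96):

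| Correlation | Error | Ratio to 5% |
|---|---|---|
| 0 | 9.75% | 1.95 |
| 0.3 | 9.5% | 1.9 |
| 0.5 | 9.1% | 1.8 |
| 0.7 | 8.4% | 1.7 |
| 0.9 | 7.0% | 1.4 |

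**Step 4. Check with the planned type of test.** Two repeated-measures ANOVAs were simulated with 50 children, three time points and 20,000 replicates. The chance of at least one significant result was 10.0% at correlation 0, 8.9% at 0.5 and 7.1% at 0.9. This agrees with step 3 within simulation error.

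**Step 5. After the change.** One named primary variable at 5% gives 5.0%. A plain split at 2.5% each gives 1 − 0.975² = 4.94% if independent and at most 5.0% under any correlation. Holm starts from the same 2.5% step and also keeps the overall error at or below 5%.

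**Step 6. Power cost under Holm.** Power of 80% at two-sided 5% means a standardised effect of 1.96 + 0.84 = 2.80. The critical value at 2.5% is 2.241, so first-step power is P(Z > 2.241 − 2.80) = 0.71. This is a lower bound, because Holm tests the second variable at 5% once the first is rejected. If the other variable is independent and also has 80% power, power is 0.712 + (0.80 − 0.712) × 0.712 = 0.775.

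**The case against.** The strongest objection is that the article never says a significant result on either variable establishes an effect on saliva. If flow rate and IgA are reported as two separate conclusions, each has the stated 5%. If both had to be significant, there would be no inflation. This stands, and the 9.75% is therefore conditional. It does not remove the point, because the article states neither of those rules and the broad aim leaves the either-one reading open.

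Three stronger readings are tempting, and the documents do not support them.

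- **That the error is simply twice the stated level.** The figure near double belongs to independent tests. No correlation is given, and both variables come from the same five-minute saliva collection, so independence is not a natural default. Up to 9.75% is as far as one can go.
- **That this is the probability of wrongly crediting the laser.** Section 2.9 is a before/after comparison, and no untreated comparison group is described. The null hypothesis tested is no change over time. A time trend from any other cause would count as a positive result whatever level is used.
- **That the planned correlations with malnutrition add a further family of errors.** Two saliva measures by two growth indices would give 1 − 0.95⁴ = 18.5%. However, the article does not say which malnutrition measure enters the correlations, the two indices come from the same child and are unlikely to be independent, and nothing presents these tests as confirmatory.

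Two further reservations are fair. Buffering capacity makes the size of the family uncertain: a third independent test would give 1 − 0.95³ = 14.3%, but section 2.9 does not list it for the before/after comparison. The registry record and Figure 1 are also not visible, so the point rests on the article text alone.

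**Conclusion.** The point holds in conditional form. The article states one primary aim, gives it two unranked variables, and sets a plain 5% level with no adjustment across them. If significance on either is taken as an effect on saliva, the chance of falsely declaring a before/after change lies between 7.0% (correlation 0.9) and 9.75% (independent tests), and it exceeds 5% at every correlation examined. The assumptions are that each variable is tested at 5%, that either result would suffice, and that the correlation lies in the range shown. The freedom to choose the headline variable afterwards does not depend on the correlation.

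This should be corrected before analysis. It does not invalidate the design. The documents motivate both variables and do not show that flow rate must be preferred to IgA, or the reverse.

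**What to change.** Before the data are analysed, the investigators should choose one of two options and state it in the aims and in section 2.9:

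1. Name either flow rate or IgA as the single primary variable, tested at two-sided 5%, and test the other confirmatorily only if the first is significant.
2. Keep both as co-equal and apply Holm across them: the smaller p-value against 2.5%, then the other against 5%.

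Under either option, state that buffering capacity and the correlations with malnutrition are exploratory.

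The change costs about one sentence in each place and needs no extra children, visits or assays. Under option 1, the second variable alone cannot carry the claim. Under option 2, a variable with 80% power at 5% has at least about 71%, or about 77.5% if the other variable is independent and equally well powered. Neither option addresses the lack of an untreated comparison group, which is a separate matter.

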## Conclusion

3

The study of salivary aspects in malnourished children and possible treatments that can be used to improve salivary quality and quantity in these children has significant social relevance, as saliva is one of the main mechanisms against infection and participates in essential functions of life, such as swallowing and the maintenance of oral health.
